## Abstract

**Introduction:**

Social isolation is common in patients with psychosis and associated with a number of negative outcomes. Programmes in which volunteers provide one-to-one support—often referred to as befriending—have been reputed to achieve favourable outcomes. However, trial-based evidence for their effectiveness is limited.

**Methods and analysis:**

This is a randomised controlled trial comparing the effects of one-to-one volunteer support with an active control condition for patients with psychosis over a 1-year period. Patients in the intervention group will receive the support of a volunteer for 1 year, who will meet them weekly and engage them in social and recreational activities. Patients in the control group will not receive support from a volunteer. In both groups, patients will be given a booklet detailing locally available social activities and otherwise receive treatment as usual. Patients, volunteers, clinicians and researchers involved in the delivery of the intervention will not be blinded to group assignment, while researchers carrying out data collection will be blinded. Data collection will be conducted at baseline, at 6 and 12 months. The primary outcome is the amount of time spent engaging in social activities per day. Secondary outcomes include symptoms, quality of life, self-esteem and costs of care. Attitudes of volunteers towards mentally ill people will be assessed. Finally, in-depth interviews will be conducted with patients and volunteers.

**Ethics and dissemination:**

The study has been approved by the National Research Ethics Service (NRES) Committee London—Camden & Kings Cross (reference 15/LO/0674). The findings of the trial will be published in open access peer-reviewed journals and in the National Institute for Health Research (NIHR) journals library, and presented at scientific conferences. In addition, findings will be summarised for a lay audience and circulated to all relevant National Health Service (NHS) and voluntary organisations.

**Trial registration number:**

ISRCTN14021839; Pre-results*.*

Strengths and limitations of this studyThe randomised controlled trial is rigorously designed to address the gap in evidence regarding the effectiveness and cost-effectiveness of one-to-one volunteer support for patients with psychosis.Experiences with the intervention of patients and volunteers will be examined.The findings may inform the practice of volunteering programmes for community patients with psychosis within different types of organisations.A number of outcomes are assessed. However, there may be different perspectives on what the most relevant outcomes of volunteer support are.The nature of the study poses a high risk of unblinding of research interviewers.

## Background

Social isolation of patients with psychotic disorders remains one of the main challenges in community mental healthcare. It has been linked to poorer clinical outcomes with respect to mental and physical health, life expectancy, engagement with treatment, and quality of life.^1^
^2^

Over the past decades, both the National Health Service (NHS) and the independent sector in the UK have used volunteer resources to support mental health patients in a wide range of areas, including so-called befriending. Although the format of befriending varies across organisations, it typically involves volunteers spending recreational time with the patient over a period of time, so as to provide them with an opportunity to socialise. This is different to so-called ‘peer support’ where patients provide support to one another, and the effects operating within such interactions might differ from those employed in befriending. Volunteers are a valuable asset to mental healthcare, uniquely complementing service provision where mental health professionals may fall short. Both clinical and social gains of volunteer support have been reported. Patients receiving befriending have reported short-term reduction of symptoms,^3^
^4^ improvements in confidence and self-esteem^5^
^6^ and increased energy and interest in going out.^7^ However, trial-based evidence on the effectiveness of these one-to-one support schemes is limited.

Against this background, we designed a randomised controlled trial (RCT) aiming to test the effectiveness and cost-effectiveness of a programme of one-to-one volunteer support for patients with psychosis. The programme is referred to as a companion scheme to avoid the term befriending misleading patients into expectations of a true friendship where some boundaries to the relationship are imposed by the scheme.^8^ The scheme is based on best practice principles from befriending organisations gathered in a study in the UK (J Silvester, S Priebe, N Giatras, *et al*.s Reflecting on rhetoric and practice in the use of human resource management with volunteers. Human Relations in preparation)^8^ and will be implemented over a 1-year period. The intervention will be compared with an active control condition. It is hypothesised that volunteer input will result in patients' increased social and recreational activities, beyond those arising directly from the time spent with the volunteer, and potentially also be beneficial with respect to social contacts, symptoms, quality of life and self-esteem.

## Methods

### Study setting and design

This is a parallel group exploratory RCT with 1:1 allocation ratio testing the effectiveness of volunteer support, specifically for patients with psychotic disorders with limited engagement in social activities. The trial compares the intervention, regular one-to-one support from a volunteer, to an active control condition in which there is no support from a volunteer. Data are collected at baseline, 6 and 12 months (figure 1). Researchers conducting outcome assessments will be blind to the allocation of patients. All the statistical analyses will be conducted blind to the participant allocation. The trial is conducted within community mental health setting in the UK.

**Figure1 BMJOPEN2016011582F1:**

Time schedule.

### Participants

#### Inclusion and exclusion criteria for patients

Inclusion criteria for patients are a diagnosis of schizophrenia or a related disorder (International Classification of Diseases (ICD)-10: F20-29); engaging in an average of <60 min per day of social activities, as assessed by the Time Use Survey (TUS);^9^ willingness to receive regular one-to-one input from a volunteer over a 1-year period; working age (18–65 years); capacity to provide written informed consent; sufficient spoken English and being in care of a community mental health team for a minimum of 1 month.

Patients are excluded if they have a severe learning difficulty, or physical disability that would require specific skills of a volunteer; have received befriending or peer support services in the past 2 years; or have a history of physical violence or abuse posing a risk to the volunteer, as assessed by the referring clinician.

#### Inclusion and exclusion criteria for volunteers

Inclusion criteria for volunteers are being at least 18 years of age; willingness to provide regular one-to-one support to a patient with a psychotic disorder over a 1-year period; sufficient command of English and criminal records showing no major convictions (eg, unspent convictions of fraud or theft; convictions of violent assault or sexual offences).

Exclusion criteria are the use of secondary mental health services as a patient currently or in the last year; having a professional role in a secondary mental health service; severe physical disability interfering with social activities; and insufficient understanding of the responsibilities and characteristics of a volunteer despite having undergone volunteer training.

### Recruitment

#### Patients

Eligible patients are identified by blinded researchers screening caseloads with clinicians in mental health teams in the community in East London, which began in July 2015. They are then approached by their clinician and asked whether they are willing to be contacted by a researcher to learn more about potentially becoming involved in a companion scheme. If they agree, a meeting is arranged at which adequately trained researchers in obtaining informed consent provides the patient with a detailed explanation of the study and a participant information sheet. If the patient agrees to participate, they are asked to sign a consent form. Their demographic information is collected and they are screened using the TUS. If the patient is found to engage in more than 60 min of social activities per day on average over the previous 4 days, they are informed that they are not eligible for the study and given £5. If the patient engages in fewer than 60 min of social activities per day, a full baseline assessment is conducted, and they are given £15 for their participation in the research interview. They receive the same amount for any subsequent follow-up interview.

Adequate enrolment will be achieved by approaching a number of community mental health teams across East London (including the London Boroughs of Hackney, Newham and Tower Hamlets). Enrolment progress will be regularly monitored, barriers identified and if needed advised sought with the Trial Steering Group.

#### Volunteers

Volunteers are recruited through advertisement of the companion scheme on job websites, volunteering websites and the volunteering section of the East London NHS Foundation Trust website; advertisement in local newspapers; information stalls at volunteering fairs and poster displays in local community centres in East London.

Interested individuals are invited to phone or email the volunteer coordinator, who provides information about the companion scheme and its requirements, including the 12-month commitment and eligibility criteria. They are provided with a participant information sheet explaining the research linked to the companion scheme and their role as research participants, and asked to complete an application form. After completing the form, they are invited for a meeting with the volunteer coordinator. At the start of the meeting, informed consent to participate in the research is taken and they complete the baseline assessment. They are informed that this assessment is for research purposes and that their answers will not have any bearing on whether or not they are accepted to participate in the scheme. The assessment collects demographic information and assesses attitudes to mental illness, and the person's self-esteem. They are given £10 for the completion of the baseline measures and receive the same amount for any subsequent follow-up interview.

On completion of the baseline, the volunteer undergoes an informal, standardised interview carried out by the volunteer coordinator to assess their suitability for the scheme. This interview explores their motivation, empathy, relationship building, organisation and communication skills, identified as key qualities in volunteers in an earlier research component of the wider research programme (J Silvester. ‘In preparation’). After this interview, they provide the necessary information for a Disclosure and Barring Service (DBS) to be undertaken. Provided that there are no issues with the DBS that would deem it unsuitable for the volunteer to work with vulnerable adults, and on receipt of two references in support of their application, they are accepted to the scheme.

### Planned interventions

#### Experimental intervention

This consists of individual patients with psychosis being enrolled in a companion scheme, whereby they are matched with a volunteer companion, who will provide one-to-one support on a weekly basis over a 1-year period. This is in addition to their treatment as usual. The main aim of the scheme is to gradually develop a trusting relationship and motivate patient to engage in social activities within local community. This will involve chatting over a cup of tea at the beginning and develop into more active social engagement such as attending workshops and events available in the local area according to patient's interests. The companion scheme is a complex intervention comprising the recruitment of suitable volunteers, their training and supervision (described below), and the regular contact between them and the patients. The format of the scheme has been informed by interviews with participants in existing befriending schemes (befrienders, befriendees and coordinators of schemes) as part of the wider research programme.

For each patient–volunteer pair, the volunteer coordinator attempts to create a match based on common interests and individual preferences, as well as practical considerations such as distance and mutual availability. A meeting is arranged to introduce the pair at the patient's home, unless the patient wishes for the meeting to take place elsewhere. This is treated as a ‘test meeting’, after which the volunteer coordinator confirms with both parties separately that they are willing to proceed with the match. The volunteer coordinator facilitates the meeting by explaining the purpose of the meetings, boundaries and ground rules and establishing common interests among the two. Both parties are provided with an activity booklet detailing free or inexpensive facilities and activities available locally (eg, parks, community centres, libraries, sports, leisure centres, galleries and museums) and are encouraged to pursue these during their contact. It is reiterated that the pair should meet weekly for at least 1 hour, and that these meetings will continue for 1 year, after which they can decide whether or not they wish to continue to meet, without being overseen by the companion scheme.

The pair subsequently meet on a one-to-one basis, without being accompanied. The volunteer coordinator provides supervision by contacting both parties within the first month and intermittently thereafter to monitor progress and identify any problems. If either party wishes to discontinue the match, the coordinator hears from both parties and attempts to resolve any issues where possible, and arranges to facilitate a further meeting between the two. If one or both parties still wish to discontinue the match, attempts are made to match both parties with another person, where practically feasible. If either party wishes to discontinue their participation in the scheme, the volunteer coordinator attempts to establish whether anything can be done to aid their continued participation, prior to formally withdrawing them from the scheme.

Every 3 months, all patients and volunteers are invited for a social meet-up (eg, brunch at a local café, a walk and picnic in a nearby park) with the aim of facilitating additional interactions between patients and volunteers. Patient–volunteer pairs are actively encouraged to meet with other pairs to facilitate wider networks and reduce the focus on an exclusively one-to-one relationship.

##### Volunteer training and supervision

Volunteers deemed suitable for the scheme (see the Volunteers of Recruitment section above) attend a mandatory training session across 2 days. The training provides a comprehensive understanding of the purpose of the scheme, and of the role of the volunteer. The importance of encouraging the patient to participate in local activities outside the home, such as those listed in the activity booklets, is emphasised throughout. Further aspects of training include understanding schizophrenia and related disorders, a questions and answers with a psychiatrist, a hearing voices simulation, a talk from a service user with lived experience of schizophrenia, maintaining confidentiality, procedures for safeguarding vulnerable people and seeking help in an emergency, communication and listening skills, and managing boundaries with the patient. In addition, practical matters such as claiming travel expenses and points of contact are addressed. On completion of training, volunteers are provided with a volunteer handbook covering all aspects of their participation in the scheme. Before meeting the patient with whom they will be matched, each volunteer is given a mobile phone and SIM card for communicating with the patient, paid for by the scheme. They are encouraged to contact the volunteer coordinator at any time. In the event of the volunteer reporting challenges in the relationship that cannot be resolved by the volunteer coordinator, they are offered a meeting with a consultant psychiatrist to discuss their concerns.

#### Active control condition

Patients in the control condition do not receive the support of a volunteer companion, and continue with treatment as usual. In addition, a meeting is scheduled with a member of the research team shortly after allocation to the control, during which the patient is given an activity booklet detailing free or inexpensive facilities and activities available in their locality (as given to patients and volunteers in the experimental condition). The main aim of the booklet is to inform patients of venues for active social engagement (eg, workshops offered in community centres and libraries, classes at sports clubs and leisure centres); however, activities with lower levels of social interactions are also included (eg, parks, galleries and museums). During the meeting, patient and researcher discuss the patient's interests and the researcher encourages the patient to attend suitable activities detailed in the booklet. This is intended to control for the effect of patients in the experimental group receiving more information about locally available activities via the volunteer.

### Outcomes

The following outcome criteria are measured at all time points (ie, baseline, 6 and 12 months), unless stated differently.

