#### Primary outcome

The primary outcome is the amount of time in minutes per day that is spent engaging in social activities, on average, over the previous 4 days. It is assessed using a shortened version of the TUS, developed by the Office for National Statistics (ONS) to examine how the general population in the UK spend their time. The measure has been previously used with patients with schizophrenia.^10^ The present version excludes any items related to social media interaction. A period of 4 days allows sufficient time for increased social activity to be detected, with reduced risk of recall bias.

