## Proposed sample size

Previous unpublished work within the wider research programme surveying 113 patients with psychosis in secondary care in East London has shown that patients tend to spend 327 min per week on average engaging in social activities (SD=480), or ∼45 min per day. Doubling this to 90 min per day would be equivalent to an effect size of 0.6 (Cohen's d). To detect such an effect on a 5% significance level with 80% power, data for 84 patients (2×42) are required. Assuming a 20% drop out rate between baseline and 1-year follow-up (as observed in similar trials with similar patient populations),^23^ a total sample size of 106 is needed.

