## Statistical analysis

### Quantitative assessments

All statistical analyses will be described in a statistical analysis plan, which will be finalised and agreed prior to any analysis or unblinding of the data. Outcomes will be compared between the intervention and control groups using linear regression models, adjusting for the baseline score of the given outcome.

All analyses will be conducted under the intention-to-treat principle, and significance testing will be at the 5% level (two-sided). Results will be presented in line with the recommendations given in the CONSORT statement extension for the reporting of RCTs.

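### The primary outcome is measured at 6 and 12 months but no primary time point is named (the design implies 12), and the stated regression applied at 12 months would not use the 6-month data

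*Protocol article*

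**What the plan says.** All passages are in the protocol article.

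- **Outcomes:** the measurement schedule reads "The following outcome criteria are measured at all time points (ie, baseline, 6 and 12 months), unless stated differently", and nothing exempts the primary outcome from it.
- **Primary outcome:** defined as average daily minutes of social activity in a four-day recall window, taken from a shortened Time Use Survey (TUS). No visit is named, and the abstract names none either.
- **Quantitative assessments:** "Outcomes will be compared between the intervention and control groups using linear regression models, adjusting for the baseline score of the given outcome". Testing is two-sided at 5% under intention to treat. A separate statistical analysis plan (SAP) is to be agreed before any analysis or unblinding.
- **Proposed sample size:** "To detect such an effect on a 5% significance level with 80% power, data for 84 patients (2×42) are required". The total of 106 is then reached by allowing for losses over the whole year: "Assuming a 20% drop out rate between baseline and 1-year follow-up".
- **Experimental intervention:** volunteer support runs for one year, so 6 months falls midway and 12 months at the end.
- **Sensitivity analysis:** patients may leave because they see no benefit, or because they have improved and see no further need. Both scenarios are to be explored.
- **Economic evaluation:** follow-up costs are combined with the primary outcome measure, again without naming a visit.

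**The concern.** There are two linked points.

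**Time point.** The time of assessment is part of what defines a primary outcome. The effect halfway through a year of volunteer contact and the effect at its end are different quantities. The sample size pays for one test. If the definition leaves the visit open, a reader cannot tell from the protocol which estimate is the trial's answer, which estimate enters the cost-effectiveness ratio, or which one should inform the larger trial that the Discussion has in view.

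**Estimator.** A linear regression of the 12-month score on arm and baseline uses only patients seen at 12 months. A patient assessed at 6 months and then lost contributes nothing to it. The protocol's two reasons for leaving both arise after baseline, and the 6-month score is the one observed value of the primary outcome that could partly reflect them.

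**Working it through.** **1. Which visit does the sample size refer to?** Inputs from Proposed sample size: d = 0.6, 5% significance (two-sided according to the analysis section), 80% power, 42 per arm, 20% drop-out to 1 year.

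- Power with 42 per arm (normal approximation): Φ(0.6 × √(42/2) − 1.96) = Φ(2.75 − 1.96) = 78.5%. The t-test gives 77.6%. At d = 0.62, which rounds to 0.6, the t-test requires exactly 42 per arm.
- Drop-out: 42/0.8 = 52.5, rounded up to 53 per arm; 2 × 53 = 106, as stated.

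The protocol's figures therefore reproduce, to rounding, as **one comparison at one time, with losses counted to 1 year**. That is a 12-month endpoint in all but name, and naming it leaves 84/106 and 5% as they are.

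**2. What if both visits were treated as primary?** The document gives no correlation between the two test statistics, so this is an assumed range. Probability of at least one false-positive result from two unadjusted two-sided 5% tests:

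| Correlation | Familywise error |
|---|---|
| 0 | 1 − 0.95² = 9.75% |
| 0.3 | 9.5% |
| 0.5 | 9.1% |
| 0.7 | 8.4% |
| 0.9 | 7.0% |

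Splitting alpha to 2.5% each would leave 69.4% power per test with 42 per arm at d = 0.6, or require 53 evaluable per arm (106 evaluable; 106/0.8 = 132.5, so 133 in total). The stated sample size makes no such provision.

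**3. What do the 6-month data add to the 12-month estimate?** With monotone loss, n6 patients seen at 6 months, n12 seen at 12 months, and correlation r between the visits given arm and baseline:

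effective n = 1 / (r²/n6 + (1 − r²)/n12)

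One illustration, with half of the lost patients seen at 6 months and r = 0.6 (both assumed): n6 = 0.9N, n12 = 0.8N, so effective n = N / (0.36/0.9 + 0.64/0.8) = N/1.2 = 0.833N, against 0.80N. The gain is about 3.3% of N.

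Per arm over a wider range, with 53 randomised, 42 seen at 12 months and 11 lost (power at d = 0.6, normal approximation, against 78.5%):

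| Seen at 6 months | r | Effective n | Power |
|---|---|---|---|
| 47.5 (half of the lost) | 0.3 | 42.4 | 78.9% |
| 47.5 | 0.5 | 43.3 | 79.7% |
| 47.5 | 0.7 | 44.5 | 80.8% |
| 53 (all of the lost) | 0.3 | 42.8 | 79.3% |
| 53 | 0.5 | 44.3 | 80.6% |
| 53 | 0.7 | 46.8 | 82.7% |

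The gain runs from 0.4 to about 4 power points.

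**4. What does each estimator require of the missing data?**

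- Regression on 12-month completers: given arm and baseline TUS, being missing at 12 months is unrelated to the 12-month value. Dependence on arm is allowed, because arm is in the model.
- Repeated-measures model on both visits: the same, given arm, baseline TUS **and the observed 6-month TUS**. Drop-out that follows a good or poor response visible at 6 months is then covered.
- Neither covers drop-out that depends on the unobserved 12-month value. The protocol's two opposite scenarios address that.

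**The case against.** The strongest reply is that the document leaves little real doubt and that the remainder belongs to the SAP. Much of this stands.

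- **Equal rank and two chances at 5%.** A reader might infer that 6 and 12 months rank equally and that each is tested as primary. The Outcomes sentence is a measurement schedule; it ranks no visits and describes no test. The abstract frames the comparison over one year, and the sample size covers one test.
- **Choosing the visit after seeing the data.** A reader might also infer this from the silence. The text points the other way: the SAP is to be agreed before any analysis or unblinding, analyses are to be blind to allocation, and no interim analysis is planned. These safeguards limit the risk, although they do not name the endpoint.
- **Discarding 6-month data.** The protocol states no such rule. It follows only if the named regression is run visit by visit. Missing-data detail may properly sit in the SAP, and baseline-adjusted regression at one visit is a standard, valid analysis.
- **Exploratory status.** The trial describes itself as exploratory, which lessens the weight of a formal familywise-error argument.

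Two things remain. The article has a dedicated section defining the primary outcome, and the visit belongs there; the SAP sentence defers the analyses, not that definition. And the protocol both names a model and describes a drop-out process that the model, applied at 12 months, does not take into account. The scenario analyses do not change the main estimate.

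**Conclusion.** The point holds in a limited form. No primary time point is named for an outcome measured at two follow-ups; the design implies 12 months, and the protocol should say so. Applied at 12 months, the stated model would leave out 6-month values that bear on the kind of drop-out the protocol itself describes.

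The size is modest. The benefit is mainly a weaker missing-data assumption. Precision improves by about 3% of N in the illustration and by roughly 0.4 to 4 power points over the range tried. These figures rest on assumed between-visit correlations of 0.3 to 0.7 and on half or all of the lost patients having been seen at 6 months; the document gives neither quantity. The 7 to 10% familywise error is conditional on both visits being tested as primary and should not be read as the trial's error rate.

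**What to change.** 1. In the primary outcome definition, state that the primary endpoint is TUS minutes per day at **12 months**, tested once at two-sided 5%, and that the 6-month contrast is secondary. Name the same visit for the cost-effectiveness analysis that uses the primary outcome.
2. In the analysis section and the SAP, estimate both contrasts from one repeated-measures model with arm, visit, arm-by-visit and baseline TUS by visit, using all 6- and 12-month data.
3. Keep both drop-out scenarios as sensitivity analyses, since the model does not deal with drop-out that depends on unobserved outcomes.

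The cost is a few sentences. No new data are needed, and sample size and alpha stay as they are. The downside is a slightly more complex model than a single-visit regression.
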